### Secondary outcomes

Severity of the overall syndrome of acute alcohol withdrawal will be monitored using the Clinical Institute Withdrawal Assessment for Alcohol (CIWA-Ar) [54]. This questionnaire will be carried out once per day for the first week, starting 24 h after drinking cessation, as in normal clinical care, then twice every 7 days (±2 days) for the following 2 weeks, and once during week 4.

The AUQ will be administered every 7 days, with the first administered 24 h after drinking cessation, to measure alcohol craving. It will be administered at 3, 6 and 12 months follow-up.

Symptoms of protracted alcohol withdrawal include anxiety, fatigue, irritability, hyperarousal and depression [18]. The sleep questionnaire evaluates sleep disturbances that are a common problem during the early weeks of abstinence. This questionnaire will be carried out every 7 days (±2 days), starting 1 week after cessation of drinking and at 3, 6 and 12 months follow-up. The Profile of mood states (POMS) [55] measures current mood covering eight factors: anxiety, fatigue, depression, anger, vigour, confusion, friendliness and elation. The POMS will be carried out every 7 days (±2 days), starting 1 week after drinking cessation and at 3, 6 and 12 month follow-up. The Snaith Hamilton Pleasure Scale (SHAPS) [56] is designed to assess an individual’s ability to experience pleasure. The SHAPS will be carried out on days 7, 14, 21, 28 (±2 days) and at 3, 6 and 12 month follow-up after cessation of drinking.

A maximum of 21 saliva samples will be collected from each participant during the trial. Seven saliva samples will be collected during the course of the day on three different occasions (day 2, 7 and 20 ± 2 days after cessation of alcohol drinking). Samples will be collected in prepared tubes and were analysed for cortisol concentrations to determine the cortisol levels prior to and following mifepristone or placebo treatment. Saliva samples will only be collected while participants are in-patients; saliva sample collection will not be taken from participants who are out-patients.

Maintenance of abstinence from alcohol and levels of relapse drinking will be measured using the TLFB, administered at preliminary screening and at 3, 6 and 12 months follow-up after cessation of drinking.

### Assessment of safety

The procedures involved in this research are unlikely to cause significant discomfort or distress to participants. All questionnaire measures and research procedures have been widely validated and used in previous research without causing any problems to participants. Mifepristone has a good safety record and has been used clinically for over 15 years for other applications. However should any distress or discomfort occur with any of the procedures trained medical and nursing staff will be available on a 24 h basis to provide help and support. All staff involved in the care of trial participants will receive training on the conduct of the trial protocol. In particular training will be provided on the detection and management of expected and unexpected adverse drug events.

The collection and reporting of Adverse Events will start following the first dose of the trial medication and will continue until the last dose of the trial medication. Reporting of Serious Adverse Events, Serious Adverse Reactions and Suspected Unexpected Serious Adverse Reactions will continue until 14 days after stopping the trial medication. All concomitant medications will be recorded until 14 days after stopping the trial medication.

Daily assessments by the clinical team to monitor for signs of nausea or fatigue that might indicate adrenal insufficiency will be made. Analysis of the plasma samples that will be taken on days 1, 7 and 14 of the mifepristone/placebo administration will ensure that the electrolyte levels remain within normal limits (sodium 135–145, potassium 3.5–5.3, chloride 95–105, urea 3.3–6.7, creatinine 40–120, all units micromoles per litre). Blood pressure checks were carried out daily during the acute withdrawal phase (10–14 days) as part of the normal clinical routine, and on day 14 if not measured on that day as part of normal clinical care. In the event of a participant self-discharging from the unit before the course of mifepristone is completed, the mifepristone/placebo treatment will be stopped and the participant will be withdrawn from the trial.

Following recruitment of the first 20 participants the Data Monitoring Committee will carry out a detailed examination of the safely data to ensure that there no problems have arisen with regard to drug safety.

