**Methods/Design:**

The study is a Phase 4 therapeutic use, “Proof of Concept” trial. The trial is a double-blind randomised controlled clinical trial of mifepristone versus inactive placebo. The trial aims to recruit 120 participants referred for an inpatient alcohol detoxification from community alcohol teams, who meet the inclusion criteria; 1) Male, 2) Aged 18–60 inclusive, 3) alcohol dependent for 5 or more years. A screening appointment will take place prior to admission to inpatient alcohol treatment units to ensure that the individual is suitable for inclusion in the trial in accordance with the inclusion and exclusion criteria. On admission participants are randomised to receive 600 mg a day of mifepristone (200 mg morning, afternoon and evening) for 7 days and 400 mg for the subsequent 7 days (200 mg morning and evening) or the equivalent number of placebo tablets for 14 days. Participants will remain in the trial for 4 weeks (at least 2 weeks as an inpatient) and will be followed up at 3, 6 and 12 months post randomisation. Primary outcome measures are cognitive function at week 3 and 4 after cessation of drinking and symptoms of depression over the 4 weeks after cession of drinking, measured using the Cambridge Neuropsychological Test Automated battery and Beck Depression Inventory, respectively. Secondary outcome measures are severity of the acute phase of alcohol withdrawal, alcohol craving, symptoms of protracted withdrawal and maintenance of abstinence and levels of relapse drinking at follow-up.

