## Methods/Design

The design of the current study is a double-blind randomised controlled clinical trial of mifepristone and inactive placebo. The study is a Phase 4 therapeutic use, “Proof of Concept” trial. Ethical approval has been granted by the London–Dulwich Research Ethics Committee (reference: 10/H0808/7) and complies with UK and European Good Clinical Practice for medicinal trials guidelines. Participants will be recruited from Community Alcohol Teams serving 5 inpatient alcohol treatment units in 3 regions of England (South London, Sussex, Kent, Hull and Barnsley). Participants will be given mifepristone/placebo for 2 weeks while they are in patients undergoing detoxification from alcohol. They will then remain in the trial for a further 2 weeks undergoing cognitive testing and questionnaires, with follow-up contact at 3, 6 and 12 months subsequent to alcohol cessation.

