### Pharmacological treatment

The duration of treatment with mifepristone/placebo is 2 weeks, while participants are an inpatients in the alcohol treatment units. The daily dose will be three 200 mg tablets a day (morning, afternoon and evening) for 7 days followed by two 200 mg tablets a day (morning and evening). These doses are based on previous studies of the effectiveness and toxicity of mifepristone.

The participants will receive normal clinical care while on the unit, and concurrent medical and psychiatric disorders will be treated as required. This includes prescription of a benzodiazepine (normally chlordiazepoxide) to protect against the tremor and convulsive aspects of acute alcohol withdrawal. Benzodiazepine treatment is normally given to patients during the first 7 to 10 days of detoxification, as required, and this treatment will not be altered during the trial. All prescriptions of any drug treatment given to trial participants will be recorded during the trial.

All participants will receive the standard care provided by the participating alcohol treatment services. This includes access to all the facilities provided by the services, including psychotherapy, pharmacotherapy, inpatient and residential rehabilitation. These services are normally provided for up to 3 months per episode of care. Participants who relapse or seek further treatment will be offered additional care, in keeping with standard clinical policies.

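### Non-serious adverse events are collected only to the last dose, leaving 14 of a completer's 28 trial days uncovered although participants are still being seen

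*Protocol article*

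**What the plan says.** The protocol article, under Assessment of safety, sets three recording windows.

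- Adverse events: collection opens once dosing has begun, and it "will continue until the last dose of the trial medication".
- Serious events, with the related serious categories named in the same sentence: "Suspected Unexpected Serious Adverse Reactions will continue until 14 days after stopping the trial medication".
- Other medicines: "All concomitant medications will be recorded until 14 days after stopping the trial medication".

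The same section says that when a participant self-discharges before finishing the course, "the mifepristone/placebo treatment will be stopped and the participant will be withdrawn from the trial".

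Under Pharmacological treatment, "The duration of treatment with mifepristone/placebo is 2 weeks". Under Methods/Design, the article says of participants after treatment: "They will then remain in the trial for a further 2 weeks undergoing cognitive testing and questionnaires". Primary outcome measures and Secondary outcomes place the following in that second fortnight: CANTAB sessions, weekly BDI-II, craving, sleep, mood and pleasure scales, and further withdrawal assessments. For outpatients, Trial status limits the withdrawal assessments to days 2 to 5.

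**The concern.** The three windows do not fit together. The protocol treats the 14 days after dosing as relevant to safety for serious events and for other medicines, yet closes non-serious collection at the last dose. If a participant develops a new non-serious complaint on day 18 and is given a medicine for it, the medicine is recorded and the complaint is not. The section asks for daily watch for nausea and fatigue as possible signs of adrenal insufficiency. Either symptom starting after the last dose falls outside adverse event collection.

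The window also depends on how long a participant stays on treatment, so a person who leaves early is observed for less time. If early leaving were more common in one arm, the crude proportion with an event in that arm would rest on less observation.

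The safety data were used for decisions. The Data Monitoring Committee was to examine them after 20 participants, and Trial status says the move to outpatient recruitment took account of that safety report. By rule, non-serious events after the last dose were not collected for it.

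**Working it through.** **Inputs from the article**

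- Treatment: 7 + 7 = 14 days (Pharmacological treatment).
- Trial period: 2 weeks on treatment and a further 2 weeks (Methods/Design), so 14 + 14 = 28 days. This matches the 4 weeks in the abstract.
- Adverse event window: first dose to last dose. Serious event and concomitant medication windows: to last dose + 14 days (Assessment of safety).

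Assumption: dosing and the 28-day period start on the same day.

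**Step 1. Coverage by day of last dose, k**

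Adverse event window = k days. Serious event window = k + 14 days. Share of the trial period covered for adverse events = k/28.

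| Last dose on day | Adverse event window | Share of 28 days | Serious event window |
|---|---|---|---|
| 3 | 3 days | 11% | 17 days |
| 7 | 7 days | 25% | 21 days |
| 10 | 10 days | 36% | 24 days |
| 14 (completer) | 14 days | 50% | 28 days |

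For a completer, 28 − 14 = 14 days (50%) have no non-serious collection. This follows from the stated windows alone.

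**Step 2. Could the varying window distort a comparison of arms?**

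The article gives no stopping rates and no event rates, so the values here are assumptions. Take the same constant event rate λ per day in both arms, with a share s of an arm stopping on day 7 for reasons unrelated to events. The expected proportion with at least one recorded event is

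P(s) = (1 − s)(1 − e^(−14λ)) + s(1 − e^(−7λ)).

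For λ = 0.05 the two terms in brackets are 1 − e^(−0.70) = 0.503 and 1 − e^(−0.35) = 0.295. With 30% stopping, P = 0.7 × 0.503 + 0.3 × 0.295 = 0.441. With 10% stopping, P = 0.9 × 0.503 + 0.1 × 0.295 = 0.483. The ratio is 0.91, although the true rates are equal.

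| Stopping, arm A v arm B | Ratio, λ = 0.02 | Ratio, λ = 0.05 |
|---|---|---|
| 20% v 20% | 1.00 | 1.00 |
| 30% v 10% | 0.90 | 0.91 |
| 40% v 10% | 0.85 | 0.87 |

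**Step 3. Rate per day at risk**

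Over a window of T days, the expected proportion with a first event is 1 − e^(−λT) and the expected days at risk are (1 − e^(−λT))/λ. Their quotient is λ whatever T is, so the ratio of rates is 1.00 in every row above. This relies on the rate being constant over time.

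**Step 4. What each remedy does to the window**

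Extending collection to last dose + 14 days gives 17 days to someone stopping on day 3, 21 to someone stopping on day 7, and 28 to a completer. That matches the serious event window but leaves the windows unequal. A fixed period to day 28 gives everyone 28 days.

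**The case against.** A reader might infer that the rule biases the safety comparison, and that it does so in favour of the worse-tolerated arm. The article does not support either inference.

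- It describes no between-arm comparison of adverse events. Safety is not among the listed outcomes or in the Statistical analysis section, and how events are summarised is commonly left to an analysis plan that is not shown.
- The rule is the same in both arms and is applied blind. It distorts crude proportions only if stopping differs between arms, and no stopping rates are given.
- An event that causes someone to stop normally occurs while they are still being dosed, inside the window, and is counted. The calculation in step 2 assumes stopping unrelated to events. It therefore shows what unequal stopping alone can do and does not describe stopping because of poor tolerability.

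A reader might also conclude that half the trial is unobserved. That goes too far. Serious events and concomitant medications are still recorded, and the weekly mood scale includes a fatigue factor, so fatigue is scored off treatment. These points stand and limit the finding.

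They do not remove the gap. A weekly mood score is not an adverse event record, and missing post-treatment non-serious events follows directly from the rule, whatever the stopping pattern.

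It is also fair to say that little can now be changed. Trial status reports 26 participants recruited by September 2014 and 1 more after outpatient approval, 27 in all, with recruitment closed in May 2015.

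**Conclusion.** The point holds as a gap in ascertainment. For a completer, 14 of 28 days (50%) have no non-serious adverse event collection. Events starting in that fortnight are missed in both arms, and a medicine given for one is recorded without it. This needs only the stated windows and the assumption that dosing starts with the trial period.

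Distortion of crude adverse event proportions is possible but not established. Under the assumed stopping imbalances the ratio falls to between 0.85 and 0.91; with equal stopping it stays at 1.00. Neither the presence, the direction nor the size of a bias in this trial can be read from the article.

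The point is worth acting on because the remedy is inexpensive. It does not undermine the trial's efficacy conclusions.

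**What to change.** Collect all adverse events over one fixed period, from first dose to day 28, for every participant regardless of when treatment stops. Ask at the weekly contacts already scheduled in weeks 3 and 4. Participants who self-discharge are withdrawn from the trial and may have no weekly contact. For them, and for others who stop early, use the same means as for the 14-day serious event follow-up, where they can be reached.

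The cost is a few more adverse event forms, and incomplete data for those who cannot be reached.

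For data already collected, report events by arm with participant-days at risk, and state that non-serious events after the last dose were not collected. This costs only reporting effort. It adjusts for unequal time at risk if the event rate is roughly constant, but it cannot recover the missed events.

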### Primary outcome measures

Cognitive ability will be measured using the CANTAB. The CANTAB has been used extensively in research and previous studies have been published that have used the CANTAB test battery in patients with depression and patients with alcohol dependence [47–52]. The CANTAB testing will compare mifepristone and placebo groups concurrently. Cognitive function measurement prior to mifepristone/placebo would not be valid owing to intoxication. A pretest will be carried out on the day before the first CANTAB testing, composed of the Motor Screening task and the Reaction time task. These two tests are designed to assess basic motor and visual skills and determine whether participants are capable of being tested on CANTAB. The CANTAB tests that will be used at the two cognition testing times (between days 13 and 20 and 21 and 28) are: visuospatial ability by Reaction Time, Pattern Recognition, Matching to Sample Visual Search, Spatial Recognition memory and Paired Associates tasks; sustained attention by the Rapid Visual Processing task; and executive function by Intra- and Extra-Dimensional Shifting, Spatial Working Memory and Stockings of Cambridge tasks.

The above CANTAB test times will enable examination of cognitive testing administration of chlordiazepoxide ceases, as benzodiazepines are well established to affect memory and learning. Urine samples taken on the day of CANTAB testing will be screened for the presence of residual chlordiazepoxide or its active metabolites, which may affect cognitive performance [53].

The BDI-II [46] will be used to record symptoms of depression throughout the trial. It will be administered at every 7 days during the 4 weeks the participant is in the trial and at 3, 6 and 12 months follow-up from cessation of drinking. The BDI-II will be administered on the day of the CANTAB testing so that the results can be used as a variable in the measure of cognitive function.

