### Statistical analysis

The null hypothesis is that there will be no differences in the results from the cognitive testing between participants who received mifepristone and those who received the placebo. Primary data analysis will be by analysis of variance (ANOVA) on the CANTAB results and Beck depression scale scores for mifepristone and placebo groups, with post hoc tests for variables likely to affect these results. Analysis will be carried out both on a per protocol basis and an intention to treat basis.

A repeated measures analysis of variance using treatment type as a between-subject factor (two levels: mifepristone and placebo) and number of times the scale is applied as the within-subjects factor (five levels) will be carried out on the Beck depression scale results. This analysis will examine changes in level of depressive symptoms over the 4 weeks of the study. The analysis on the results from the BDI-II will compare the depressive symptoms prior to mifepristone/placebo with the scores during the four test weeks. This will provide information about whether or not mifepristone alters the progression of such symptoms and enable effect sizes to be calculated for such multiple comparisons in a full trial.

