### Trial status

Recruitment for the trial began in September 2012 and was completed in May 2015. A total of 26 participants were recruited between September 2012 and September 2014. The trial experienced several challenges in recruitment over this 2 year period including retendering of NHS addiction services and the closure of NHS specialist addiction units at participating research sites. In September 2014 the decision was made to recruit participants who were completing their detoxification as an outpatients as well as an inpatients, to increase the number of potential participants. This decision was made following advice from the Trial Steering Committee and the Data Monitoring Committee and the results of the safety report following recruitment of the first 20 participants. Approval from the MHRA and local Research Ethics Committee to recruit participants completing their detoxification as outpatients was granted in November 2014. The study protocol was largely unchanged for outpatient recruitment, with the following exceptions;Saliva sample collection was removed as it was not possible to gain reliable waking samples if participants were not an inpatient.CIWA assessments were only completed for days 2–5 as there were insufficient staffing resources to complete these assessments at a weekend.Plasma samples taken on days 7 and 14 were taken on days 7 and 14 +/− 2 days to allow for times when they fell on a weekend.

Following approval to recruit participants completing their detoxification as outpatients as well as those completing a detox as inpatients only 1 further participant was recruited. Completion of the final 12 month follow-up will be completed in May 2016.

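### Withdrawing self-dischargers from the trial leaves the promised intention-to-treat analysis without their CANTAB scores and later BDI-II scores

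*Protocol article*

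**What the plan says.** All references are to the Protocol article.

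- Assessment of safety: for a participant who self-discharges from the unit before the course is complete, "the mifepristone/placebo treatment will be stopped and the participant will be withdrawn from the trial". One sentence both stops medication and ends participation.
- Pharmacological treatment: "The duration of treatment with mifepristone/placebo is 2 weeks".
- Primary outcome measures: CANTAB is given at "the two cognition testing times (between days 13 and 20 and 21 and 28"), and there is no baseline because "Cognitive function measurement prior to mifepristone/placebo would not be valid owing to intoxication". For the BDI-II, "It will be administered at every 7 days during the 4 weeks the participant is in the trial", and again at 3, 6 and 12 months.
- Statistical analysis: "Analysis will be carried out both on a per protocol basis and an intention to treat basis". The BDI-II is to be analysed by repeated-measures ANOVA with the "number of times the scale is applied as the within-subjects factor (five levels"), comparing the pre-treatment score with those of the four test weeks.
- Secondary outcomes: abstinence and relapse drinking come from the TLFB at 3, 6 and 12 months.
- Trial status: 26 participants were recruited by September 2014 and one more after outpatients were allowed. "Completion of the final 12 month follow-up will be completed in May 2016".

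**The concern.** Stopping study medication and leaving the trial are different events. An intention-to-treat comparison needs outcomes from everyone randomised, including those who stop treatment. Here the same event that stops treatment also stops outcome collection, so the participants who separate the intention-to-treat set from the per-protocol set are those without the outcome.

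Leaving a detoxification unit early is unlikely to be unrelated to what the trial measures. The Background links depression to a greater tendency to relapse, and reports a clinical trial in which mifepristone reduced craving and drinking. If the drug changes who stays, a comparison among those who stay is no longer a comparison of the groups as randomised. The article also intends the trial to supply effect and variance estimates for a later full trial, so any distortion would carry forward.

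**Working it through.** The plan gives no figure for self-discharge, so there is none to reproduce. The check has three steps.

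**1. What a self-discharger contributes if the rule is followed**

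- CANTAB: first window opens on day 13, with no earlier measurement. Leaving before about day 13 gives 0 of 2 scores and no baseline from which to impute.
- BDI-II: five scores are planned, one before treatment and four weekly. Taking the weekly scores at days 7, 14, 21 and 28 (my reading of every 7 days), leaving before day 7 gives 1 of 5 and leaving between days 7 and 14 gives 2 of 5. A repeated-measures ANOVA in its usual form uses only participants with all five, so these scores would drop out.
- TLFB and BDI-II at 3, 6 and 12 months: none, if being withdrawn from the trial covers follow-up.
- Safety: the same section continues serious adverse event reporting and concomitant-medication recording to 14 days after medication stops. That is not collection of the efficacy outcomes.

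**2. How large a bias could be (all rates assumed)**

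Suppose no true effect, an outcome with SD 1, and participants leaving when a latent tendency correlated ρ with a worse outcome passes a threshold. With a share p withdrawn, the mean among stayers is shifted by ρ·φ(c)/(1−p), where c = Φ⁻¹(p). The factor φ(c)/(1−p) is 0.195, 0.350, 0.497 and 0.644 at p = 10%, 20%, 30% and 40%. The bias b is ρ times the difference of the two factors; for example, 0.5 × (0.497 − 0.195) = 0.15.

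| Withdrawn, arm A v arm B | b, ρ = 0.3 | b, ρ = 0.5 |
|---|---|---|
| 20% v 20% | 0 | 0 |
| 10% v 20% | 0.05 SD | 0.08 SD |
| 10% v 30% | 0.09 SD | 0.15 SD |
| 20% v 40% | 0.09 SD | 0.15 SD |

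The arm that loses more looks better.

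The two-sided type I error is 1 − Φ(1.96 − b/SE) + Φ(−1.96 − b/SE), with SE = √(1/n₁ + 1/n₂) and n the number left in each arm. At the planned 60 per arm, the unequal rows give 5.6% to 11.3%. At the recruited size of about 27 (13.5 per arm, equal split assumed), they give 5.1% to 6.4%. The worst case there is 10% v 30% with ρ = 0.5: n = 12.15 and 9.45, SE = 0.434, b/SE = 0.348, error 6.4%. At this size the harm is mainly to the estimate, not to the error rate.

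**3. Relapse, and what counting leavers as relapsed can do (assumed rates)**

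Let 30% of placebo and 15% of mifepristone participants leave, and let 50% of stayers relapse in both arms.

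- If all leavers relapse, true relapse is 0.30 + 0.70 × 0.5 = 65% v 0.15 + 0.85 × 0.5 = 57.5%. Stayers alone show 50% v 50%. Counting leavers as relapsed recovers 65% v 57.5% exactly.
- If leavers relapse at the same 50%, the truth is 0.30 × 0.5 + 0.70 × 0.5 = 50% v 0.15 × 0.5 + 0.85 × 0.5 = 50%. Counting leavers as relapsed then creates a 7.5-point difference.

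The rule for leavers is therefore useful as a sensitivity analysis but does not replace contact with them.

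**The case against.** The other side has five good points.

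- **Follow-up loss is inferred.** The Abstract, Methods/Design and Primary outcome measures use being in the trial for the four-week phase and mention the 3-, 6- and 12-month contacts separately. Withdrawal from the trial need not end those contacts. This stands: loss of long-term follow-up is the plain reading, but not certain.
- **Bias is not shown.** A reader might infer that randomisation no longer protects the comparison, or that the results will be biased. The documents do not support that. They give no self-discharge rate and no reasons for leaving, and equal, similarly motivated withdrawal leaves the difference unbiased. They do not report that anyone has self-discharged.
- **BDI-II scores exist.** A screening score and any weekly scores before departure are available, and a different model could use them. This stands, so a reader should not infer that the intention-to-treat and per-protocol sets are the same for BDI-II.
- **CANTAB after relapse may be invalid.** The trial asks about memory during abstinence and treats testing under intoxication as invalid. Retained leavers who are drinking may be untestable or may answer a different question. This stands and limits the CANTAB part of the fix.
- **The time for change has largely passed.** Recruitment is closed at about 27, so weeks 1 to 4 cannot be recovered, and calculations of power at the planned 120 no longer bear on this trial.

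A sixth argument, that the unseen analysis plan may deal with this, does not succeed. How the intention-to-treat set is defined can be left to that plan. But the rule concerns data collection, and an analysis plan can model or impute an outcome that was never collected but cannot recover it.

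**Conclusion.** The concern holds in a limited form. As written, the rule takes early self-dischargers out of outcome collection, so the promised intention-to-treat analysis is in effect a completer analysis for CANTAB and largely so for the five-level BDI-II ANOVA. For the 3-, 6- and 12-month TLFB and BDI-II, the same loss is likely but the wording leaves it open.

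The consequence is a risk of bias if self-discharge differs between arms in rate or reason, which the article's own Background makes plausible. Its size and direction cannot be settled from the documents. The range of 0.05 to 0.15 SD rests on assumed withdrawal rates of 10% to 40%, assumed correlations of 0.3 to 0.5, and leavers having worse outcomes. With equal rates and the same correlation in both arms it is zero.

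**What to change.** Leave the medication-stopping rule as it is and separate it from follow-up. State that a participant who self-discharges stays in the trial for BDI-II, TLFB and, where he can validly be tested, CANTAB, with drinking status recorded at testing, unless he withdraws consent. Say explicitly whether the 3-, 6- and 12-month contacts continue. Any full trial built on this one should carry the same wording.

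For this trial, the practical steps are:

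1. Seek the remaining TLFB and BDI-II follow-up contacts from any self-dischargers, where consent allows.
2. Analyse all randomised participants with available data, for example with a likelihood-based mixed model for BDI-II, so that scores before departure are used. Add a sensitivity analysis counting leavers as relapsed.
3. Report the number and timing of self-discharges by arm, and do not describe the CANTAB analysis as full intention to treat where outcomes were not collected.

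The cost is a short amendment and a few extra contacts using existing procedures, plus some CANTAB sessions that may prove unusable after relapse. The gain is limited: 26 of the 27 participants were recruited by September 2014, so their 12-month contacts fall due by about September 2015, and few scheduled contacts may still be open before follow-up ends in May 2016.
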